#### Static motor control intervention

The supervised therapy sessions and home exercises of the standard static motor control intervention will consist of exercises in which patients will be instructed to contract their m. Transversus Abdominis during a variety of postures and body movements while keeping their spine in neutral position, i.e., trying to make as little spinal movements as possible. The exercises will be offered with increasing intensity, difficulty, and complexity per week by using a variety of postures, movements, and exercise equipment such as a balance board or foam pad to stand on. Modifications in progression of the patient will be registered by the treating therapist. The home exercises will be covered during the supervised sessions to adjust the load level of these exercises to the capacity of the patient if necessary.

#### Sensor-based movement control intervention

For the supervised therapy sessions of the Sensor-Based Movement Control intervention, Valedo^®^ Motion 2.0 (Hocoma) will be used. Valedo Motion is a medical device on which a patient can play games controlled with spinal movements. Spinal movements are tracked using three small inertial measurement units (IMUs), placed on the pelvis (S1), thorax (sternum) and thoracolumbar (L1) area of the spine. The orientation of these sensors is streamed to a laptop and used in real-time to control several games. These games are displayed on a laptop and invite the player to make controlled (in terms of movement direction, speed, and amplitude) movements of the spine in various postures (e.g., standing, sitting or on hands and knees). During the first few sessions, the workflow of the hardware and software will be demonstrated and explained by the therapist. It is expected that the patient can perform the set-up independently (under supervision of the therapist) after these two sessions. During each session, patients will play four different games. Before each session, the patients spinal range of motion around the three anatomical axes will be determined using the software. The standard protocol for games throughout the sessions are pre-set by the investigators and will be offered with increasing intensity, difficulty, and complexity. Modifications in progression of the patient will be registered by the treating therapist. The home exercises resemble the movements and postures of the Valedo games of that week. These exercises will also be adjusted to the capacity and need of the patient by the therapists, for example by changing the game duration or difficulty level of the game or by using exercise equipment.

### Multidisciplinary rehabilitation programme

All patients of the study will be enrolled in a multidisciplinary rehabilitation programme. This is a standard care programme at the MRC for patients with chronic low back pain which has a focus on increasing the activity and physical level, education about back pain, healthy lifestyle and awareness of the body and physical limits. The programme follows a protocol in which the number, duration and content of the therapies is fixed. During this 12-week programme, they will receive multiple therapy sessions for 3 days a week. The programme mainly consists of physiotherapy (19 individual sessions of 30 min), occupational therapy (19 individual sessions of 30 min), sports therapy (20 group sessions of 60 min consisting of fitness, swimming and game sports) and 4 group sessions of body awareness. In the *first* week, pain-education is given by a psychologist and social worker and, if necessary, further individual guidance is provided once a week. The therapists of these disciplines are discouraged, but not prohibited, to focus their interventions on static motor control or spinal movement control exercises and they will not have access to Valedo^®^ Motion during these therapy sessions. Moreover, they are request not to compensate for the given intervention (e.g., providing more dynamic exercises for patients in the static movement control group). The therapists will not be restricted in their therapy programme in any other way. It will not be registered to what extent static motor control or movement control exercises are provided during these therapy sessions.

### Data collection and outcome measures

Patients will be tested at two instances, once before (T0: week 1) and once after the intervention (T1: week 10). In addition, we will contact them by email at 6- and 12-months follow-up (T2: week 26 & T3: week 52). Per follow-up moment, patients receive a maximum of 2 emails and 1 letter, to enhance completion of the follow-up. Table 2 highlights the measures collected at each point in time. At the start of the intervention study, patients' characteristics will be recorded to enable comparison of baseline characteristics of both groups.

**Table 2 T2:** Overview of outcome measurements in this study.

	**Intervention**		**Follow-up**	
	**T0**	**T1**	**T2**	**T3**
**Patient characteristics** Age, height, weight, BMI, gender, duration of complaints	X			
**Questionnaires** RAND-36, FABQ, NRS, ODQ, RMDQ	X	X	X	X
**Movement control assessment** Tracking tasks, clinical spinal movement control tasks, repetitive motion tasks and gait trials	X	X		
**Therapy adherence** EARS		X		

T0: week 1; T1: week 10; T2: week 26; T3: week 52.

#### Primary outcome

Our primary outcome measure is movement control of the spine. This will be quantified using three spinal movement controlled tracking tasks and a clinical movement control test battery. The movement controlled tracking tasks are based on the tracking task used in the study of Willigenburg (12). The tracking tasks used in this study consist of one flexion-extension, one lateral flexion and one rotation task, and will be performed at T0 and T1 with 3 Valedo Motion inertial measurement units (IMUs) attached at the right thigh, pelvis (at S1 level) and at the sternum level. During these tasks, patients will be instructed to move their spine in order to keep its real-time representation (on a laptop screen located in approximately one meter in front of them at eye level) within a moving target. Patients are in a seated position. The patient's pelvis will be fixated with a frame, which will be used to guarantee that the spinal angle is changed without any hip motion. Each trial will last 2 min and 40 s, with the first 40 s being for learning the task, and the following 2 min for the actual measurement. During the flexion/extension task, the vertical position of the target on the screen will vary between values that correspond to 20 degrees trunk flexion and 10 degrees trunk extension. During the lateral flexion and rotation task, the horizontal position of the target on the screen will vary between values that correspond to 10 degrees left and 10 degrees right lateral flexion or rotation. In each tracking task, the target will follow a multi-sine with a main frequency of 0.025 Hz (one cycle each 40 s). All these movement excursions are within the maximum range of the tracking task that was used by Willigenburg (12). Formula 1 and Table 3 describe the movement profile of the tracking target in each task, illustrated in Figure 3. The reliability or minimal detectable changes of this movement control measurement is unknown.

**Table 3 T3:** Used offset and ROM for each movement plane and characteristics of the multi-sine-wave.

Movement plane	**Off**set	**ROM**	Excursion
Sagittal (flexion)	5	30	−10/20
Frontal (lateral flexion)	0	20	−10/10
Transversal (rotation)	0	20	−10/10
Sine no.	***Ampl***itude (%)	***f***requency (Hz)	**φ**: Phase (rad)
‘Main' Sine #1	80	0.025	0.00
Sine #2	10	0.215	0.22
Sine #3	6	0.185	0.14
Sine #4	4	0.250	0.84

Bold text in the table corresponds to bold text in Formula 1. ROM: Range of Motion.

**Figure 3 F3:**
[figure not shown]
Position of the tracking target over time. The blue line represents the position of the tracking target over time. The black dashed line represents the offset of the target trajectory. The green dotted lines represent the movement excursion during each task. The imposed movement excursion during the lateral flexion and rotation task was symmetrical. During the flexion/extension task the movement excursion was larger in the flexion direction (i.e., 20 degrees) than in extension direction (i.e., 10 degrees).

***Formula 1: Used offset and ROM for each movement direction and***
***characteristics of the multi-sine-wave*. ***Bold text corresponds to bold text in*
*Table 3**. t* = *time, starting at the beginning of the tracking task*.

$$\begin{array}{l} Target_{plane}(t)=Off_{plane}+\frac{ROM_{plane}}{2}\times \sum_{i_{Sine}=1}^{4}Ampl\left(i_{Sine}\right)\\ \;\times sin\left(2\pi f\left(i_{Sine}\right)t+\varphi \left(i_{Sine}\right)\right) \end{array}$$

The tracking error (average absolute deviation from imposed trunk angle) around the imposed movement axis of the three tasks will be reported as average tracking error (in degrees).

The clinical movement control test battery of the lower back will be the tests of Luomajoki et al., (19, 20). This test battery consists of six active movement control tests in which the patient performs each movement once. The test will be recorded on video from the front or side (depending on the movement) using a video-recorder and two blinded experienced (>10 years) physiotherapists will rate the performance of the tests from the recordings. These therapists will be instructed by the investigators how to score this assessment prior to the ratings. The total score can range from 0 to 6, indicating the number of tests with clear movement dysfunction. The final score of the test battery will be calculated as a mean of the two raters.

#### Secondary outcomes

Spinal movement will also be measured in other movement tasks as secondary outcomes.

– Gait trials: Cycle-to-cycle variability of spinal rotations (measured in degrees) will be measured during gait on a treadmill. The tasks consist of walking for 5 min at three different walking speeds, with a small pause for IMUs calibration in between: one at comfortable walking speed, one at 6 km/h (“fast walking”) and one at 2 km/h (“slow walking”) (25).– Repetitive bending task: Cycle-to-cycle variability of spinal flexion (measured in degrees) will be measured during a repetitive bending task. Patients will touch the sides of a box (2 cm x 30 cm x 30 cm) that is in front of them, at their tibial tuberosity height, for 40 times. Prior to the task, a video of the task executed at 0.92 Hz is shown to give patients a visual demonstration of the expected task movement and frequency.– Repetitive rotation task: Cycle-to-cycle variability of spinal rotation will be measured during a repetitive standing rotation task. Patients will touch two lateral targets with their contralateral hands, alternating them for 80 times (40 times each). Targets' positions are at the patients' homolateral arm distance, at their shoulders' height, and rotated 45° relative to their anteroposterior axis. A video of the task executed at 0.62 Hz is shown to give patients a visual idea of the task's expected movement and frequency.– Self-developed movement control test of the lower back. During this test, patients will perform 4 movements consisting of 3 continuous repetitions of a pelvic tilt, flexion/extension, lateral flexion and rotation of the spine. First, all 4 movements will be performed seated and next, these same 4 movements will be performed in standing position resulting in 8 tests. Each test will be scored in “correct” (two points): low back or pelvic movement is performed fluently and isolated (thoracic movement in absence of pelvic movement or vice versa); “partial correct” (one point): the movement is performed not fluently *or* insufficiently isolated; or “not correct” (zero points): the movement is not performed fluently nor isolated. A higher score represents a better movement control of the lumbar spine. The test will be recorded on video and rated in the same manner as the movement control test battery of Luomajoki. This test was developed because in the test battery by Luomajoki et al. (19, 20) no movement of the spine is requested during most tests. In fact, in five out of the six imposed movements, the subjects are instructed explicitly to not move the lumbar spine.

We have no specific hypotheses regarding the aforementioned movement variability outcomes. These outcomes were primarily assessed as part of a case control study (see pre-registration https://osf.io/3dr58).

The tracking tasks, gait trials and repetitive motion tasks will be performed in quasi-random order at baseline and post-intervention measurements.

In addition to the movement control outcomes, patient reported outcome questionnaires will be assessed at baseline, post-intervention and at follow-up. The patient reported outcomes measured in this study will be: Exercise Adherence Rating Scale (EARS) (26), Dutch version of the Oswestry Disability Index (ODI) 2.1a (27), Dutch version of the Roland Morris Disability Questionnaire (RMDQ) (28, 29), three scores of Numeric Rating Scale (NRS) for Pain; the average and maximum pain intensity over the past 7 days and current pain intensity (29), Dutch version of Fear Avoidance Beliefs Questionnaire (FABQ) (30), Four scales of the Dutch version of the RAND-36 (Physical functioning, mental health, general health and pain) (31).

### Data management

Patients will receive a unique three-digit number that will be used on all forms (except the informed consent form) used in this study. Only the principal investigators will have access to the key of this code list. The informed consent and patient related forms will be stored separately from the other forms and will be stored for 15 years. Video-recordings of the clinical movement control test battery will be stored locally at the MRC. Only the principal investigators will have access to these recordings. The recordings will be scored by two independent physical therapists, under supervision of a principal investigator.

### Statistical analysis

To evaluate if movement control of the spine changes differently between groups over the course of the treatment, repeated measures ANOVAs will be used to evaluate if a significant Group x Time interaction effect exists for the tracking error during each tracking task separately, the average tracking error of the tracking tasks and the total score of the clinical movement control test battery. The main effects of Group and Time will also be assessed using the same ANOVA. In addition to the total score of the clinical movement control test battery by Luomajoki et al. (19, 20) the performance on the individual tests that comprise the test battery will also be reported per group at T0 and T1.

Secondary study parameters will be assessed in the same manner as described above without correction for multiple testing, because these analyses are of an exploratory nature, and we want to limit the probability of type 2 errors. For the questionnaires that will be filled out on more than two occasions, we will perform *post-hoc* independent t-tests, with LSD correction, comparing results between groups at each point in time. Patient characteristics and all questionnaires filled out during the first testing day will be compared between groups using independent sample *t*-tests without correction for multiple testing to evaluate if differences existed at baseline. Statistical analyses in this study will not be adjusted for baseline differences between groups, as recommended by de Boer et al. (32). Independent of normality, parametric statistics will be used in this study and the alpha level will be set at 0.05 (33).

Data from patients who attended less than 10 sessions are not included in the statistical analysis. In addition, the data is also not included if patients have dropped out of the study before T1.

Missing data will be handled by using complete case analysis with all repeated measures ANOVAs between T0 and T1 and independent *t*-tests between T0, T1 and T2 and between To, T1, T2 and T3.

All statistical analyses will be performed using R version 4.1.1.

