Movement control over less centrally located joints, such as the elbow or knee, can be trained using functional tasks, like bringing a spoon to the mouth or kicking a ball toward a pylon. The success of the execution (not spilling the soup or knocking over the pylon) can be used as an indication of good control over the movement of the joint. Providing meaningful feedback on spinal movements is more complicated. Sensors that measure spinal movements can offer a solution (14). There are several sensor-based training systems available on the market, but currently only a few randomized controlled trials incorporating these technologies have been published (15, 16). These sensor-based training systems can be used to offer accurate real-time feedback on spinal movements, which could help to improve spinal movement control. These systems provide the possibility to train spinal movement control relatively independent without the need of intensive supervision and/or a highly experienced therapist (17). Moreover, the training sessions are relatively easy to standardize and the progression from simple toward complex movements can easily be adapted to each patient's abilities and needs. The sensor-based exergames could be more engaging and motivating than conventional motor controlexercises, which might increase therapy adherence (18).

This paper describes the protocol for a randomized controlled trial to evaluate if a sensor-based movement control intervention enhances movement control of the spine in low back pain patients to a greater extent than a standard static motor control intervention. We will assess movement control using a custom made spinal movement controlled tracking task and a clinical test battery by Luomajoki et al. (19, 20). We hypothesize that a sensor-based movement control intervention will enhance movement control of the spine in low back pain patients measured by spinal movement controlled tracking tasks to a greater extent than a standard static motor control intervention. The majority of the tests in the clinical test battery by Luomajoki et al. (19, 20) involve no spinal movement, hence we hypothesize that the static motor control group will improve more on this outcome than the sensor-based movement control group.

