### Randomization, blinding and treatment allocation

This study is quasi-randomized and non-concealed. Patients will be screened in the first week of the multidisciplinary rehabilitation programme (2 weeks prior to baseline data collection). Enrolment and allocation will be 1 week prior to baseline data collection after consent of the patient. Patients will be enrolled and allocated to each intervention by one of the investigators ([name]) based on the starting date of the multidisciplinary rehabilitation programme. The research team has no influence on the starting date of each patient. If two patients start on the same date, allocation order will be alphabetically (based on the patients last name). The first five patients were allocated to the static motor control group, followed by five patients in the sensor-based movement control group and so forth until 30 patients have completed each intervention. This random allocation sequence was chosen by the investigators to keep group therapy planning feasible. Patients and therapists will not be blinded as this is practically impossible, however they will not be informed about the hypotheses of the study. The primary study outcome (spinal movement tracking error) will be calculated using a computer algorithm (custom made in D-flow, Motek, Amsterdam, The Netherlands) that will work independent of treatment allocation. Investigators involved in the statistical analysis will not be blinded to group. The clinical movement control battery tests will be recorded on video and scored by two examiners that are blinded to time (before/after intervention) and allocation.

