## Discussion

In this study, the effect of a sensor-based spinal movement control intervention on the movement control of the spine in low back pain patients over the course of a multidisciplinary rehabilitation programme will be compared to the effect of conventional static motor control exercises. In addition, we aim to evaluate the effect of the intervention on disability, pain intensity, fear avoidance beliefs and health related quality of life. Finally, therapy adherence will be compared between the interventions. Sensor-based exergames are a relatively new tool to train spinal movement control using meaningful and engaging feedback. To our acknowledge, this is the first study which evaluates if sensor-based exergames training influences movement control of the spine in low back pain patients to a greater extent than static motor control training.

Currently, there is no gold standard to assess movement control of the spine. Therefore, we will analyse our main outcome with three different assessments: [1] sensor-based tracking tasks on a laptop, based on a tracking task from Willigenburg et al. (12), [2] the clinical movement control test battery of Luomajoki et al. (19, 20) and [3] a self-developed clinical movement test battery. Because these tests are performed in the same subjects at the same moment, the results of this study could provide us more insight in how to assess movement control of the spine. The reliability and minimal detectable changes of the movement control tracking tasks and the self-developed clinical movement test battery are not available which may bias the outcome of the study.

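### The primary outcome is stated inconsistently and tested five times at 0.05 with no deciding test, although the sample size is built for one interaction

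*Protocol article*

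**What the plan says.** The protocol describes the primary outcome in several places, and they do not match.

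- **Randomization, blinding and treatment allocation:** tracking error alone. "The primary study outcome (spinal movement tracking error) will be calculated using a computer algorithm".
- **Primary outcome:** the outcome is movement control of the spine, and "This will be quantified using three spinal movement controlled tracking tasks and a clinical movement control test battery".
- **Discussion:** "we will analyse our main outcome with three different assessments". The third of these is the self-developed movement test.
- **Secondary outcomes:** the self-developed test sits in the list that opens with "Spinal movement will also be measured in other movement tasks as secondary outcomes".

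The Statistical analysis section plans repeated measures ANOVAs for the Group x Time interaction on five measures, the last being the battery total: "tracking error during each tracking task separately, the average tracking error of the tracking tasks and the total score of the clinical movement control". Alpha is 0.05. Correction for multiple testing is expressly waived for the secondary parameters, on the ground that they are exploratory. For the five tests above, nothing is said about correction, order or which test decides.

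The Sample size section plans for one Group x Time interaction (54 patients, 95% power) and uses tracking error as its only worked outcome. The Introduction predicts that the sensor-based arm will do better on tracking. For the clinical battery it predicts the reverse: "we hypothesize that the static motor control group will improve more on this outcome".

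**The concern.** A trial sized for one test should say which test that is. Here the sample size matches a single interaction and the analysis section lists five, all attached to the outcome called primary. Two things are at stake.

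The first is the false-positive rate. If a significant result on any of the five may be presented as a finding on the primary outcome, the chance of such a result when the arms do not differ is above 5%. The Randomization section also says that the investigators doing the statistical analysis know the group allocation, so the choice of the leading result should be fixed in advance.

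The second is interpretation. Two parts of the same primary outcome are expected to move in opposite directions. If both predictions come true, each arm is ahead on part of the primary outcome, and the document does not say what that means for the aim.

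**Working it through.** **Step 1: reproduce the planned sample size.** Inputs from Sample size and Statistical analysis: effect size 0.25, two groups, two time points, alpha 0.05, power 95%, N = 54. The effect-size metric and the correlation between T0 and T1 are not stated. Reading 0.25 as Cohen's f and assuming a correlation ρ = 0.5:

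λ = f² × N × m / (1 − ρ) = 0.0625 × 54 × 2 / 0.5 = 13.5, with 1 and 52 degrees of freedom.

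Power is 95.0%, so N = 54 is reproduced for **one** interaction at the full 0.05. It depends on ρ: the same target needs 76 patients at ρ = 0.3 and 34 at ρ = 0.7.

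**Step 2: count the tests.** Three tasks + their average + battery total = 5.

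**Step 3: chance of at least one false positive.** The average is formed from the same three tasks (Primary outcome section), so the tests are dependent and a simulation is needed. Settings: 27 per arm, no true difference, 100,000 trials per row, normal change scores, and two-sided t tests on change scores (equivalent to the 2 x 2 interaction F test). The protocol gives no correlations, so all of those below are assumptions.

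| Correlation between tasks | Battery with tasks | Any of five significant | Only hypothesised directions |
|---|---|---|---|
| 0 | 0 | 20.5% | 10.4% |
| 0.3 | 0 / 0.2 | 18.9% / 18.5% | 9.6% / 9.8% |
| 0.5 | 0 / 0.3 | 17.2% / 16.9% | 8.7% / 9.0% |
| 0.7 | 0 / 0.3 | 15.7% / 15.3% | 8.1% / 8.1% |
| 0.8 | 0 / 0.5 | 14.3% / 13.4% | 7.3% / 7.4% |
| 0.9 | 0 / 0.6 | 13.0% / 11.7% | 6.6% / 6.8% |

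The last column counts tracking results that favour the sensor arm and battery results that favour the static arm. As a check, the average tracking error alone was significant in 4.9% to 5.1% of trials. The self-developed test is not counted; treating it as primary, as the Discussion does, could only raise these figures.

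**Step 4: what each remedy does to error and power** (f = 0.25, ρ = 0.5).

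| Primary tests | Alpha per test | Power at N = 54 | N for 95% |
|---|---|---|---|
| Average tracking error only | 0.05 | 95.0% | 54 |
| Two, Bonferroni | 0.05 / 2 = 0.025 | 91.0% | 64 |
| Five, Bonferroni | 0.05 / 5 = 0.01 | 83.7% | 76 |

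Keeping the average and the battery as two uncorrected tests gives a false-positive chance of 8.8% to 9.9%.

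**Step 5: read the possible result patterns against the text.**

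- All five favour the same arm: the aim is answered whichever definition applies.
- Tracking favours the sensor arm and the battery favours the static arm (the predicted pattern): each hypothesis is supported, but no rule says what this means for the primary outcome as the Primary outcome section defines it.
- One plane is significant and the average is not, or the reverse: no rule says which counts.

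**The case against.** The strongest reply is that the intention can be recovered. The two operative sections, Primary outcome and Statistical analysis, agree on tracking tasks plus battery. The statement in the Randomization section is a parenthesis in a paragraph on blinding, and the Discussion sentence responds to the lack of a gold standard. The hypotheses are specific to each outcome, so a static-arm win on tracking would not be counted as a success. Multiplicity rules may also stand in a full protocol or analysis plan that is not shown.

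Much of this stands, and it rules out several stronger readings that a reader might infer:

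- **An error rate of up to 23%.** The formula 1 − 0.95⁵ = 22.6% needs five independent tests. The average is a function of the three tasks, so that cannot occur; with all other correlations at zero the figure is 20.5%.
- **No result could settle the aim.** Concordant results would settle it.
- **An explicit refusal to correct the primary tests.** The waiver concerns secondary parameters. For the five tests, the absence of correction is read from silence together with the flat alpha of 0.05.
- **A battery that does not measure movement control.** The protocol notes that five of its six tests ask for no lumbar movement. It also defines control in relation to the demands of the task, and keeping still can be such a demand. The text does not decide the matter.

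The reply does not remove the conflict itself. The statements of the primary outcome cannot all be right. Where the two operative sections agree, they agree on five tests with no deciding one, which does not fit a sample size for one interaction.

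**Conclusion.** The point holds. The primary outcome is stated inconsistently within the document, and five interactions on it are tested at 0.05 with no deciding test, hierarchy or stated correction, against a sample size for one. The chance of at least one false positive among the five is about 12% to 20% for assumed task correlations from 0.9 to 0, and about 7% to 10% if only results in the hypothesised directions count. These figures rest on assumed correlations, normal change scores and 27 patients per arm. Mixed or opposite results, including the split that the authors predict, have no prespecified interpretation. This should be corrected before outcomes are compared by arm.

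**What to change.** Name the Group x Time effect on the average tracking error as the single primary test at two-sided 0.05. This agrees with the Randomization section and with the outcome used in the Sample size section, and it leaves N = 54 at 95% power as planned, on the same unstated f and ρ. List the three plane-specific errors and the clinical battery as secondary. Keep the directional hypothesis for the battery, reported as a secondary result. Align the wording in Randomization, Primary outcome, Secondary outcomes, Statistical analysis and Discussion, so that the self-developed test is secondary throughout.

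A prespecified order of testing or an alpha split would also cure the defect. A split would cost power or patients, as the second table in the working shows.

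The cost is that the battery loses its primary status. No new data are needed. Because enrolment began on 17 May 2021 and data collection is in progress (Study setting), the change is an amendment and has to be communicated to the ethics committee, the funder, the registry and the sponsor, as the Dissemination section requires.
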